## Abstract

**Background:**

The transition to parenthood represents a critical life period with psychosocial, and behavioral changes and challenges for parents. This often increases stress and leads to unhealthy weight gain in families, especially in psychosocially burdened families. Although universal and selective prevention programs are offered to families, specific support often fails to reach psychosocially burdened families. Digital technologies are a chance to overcome this problem by enabling a low-threshold access for parents in need. However, there is currently a lack of smartphone-based interventions that are tailored to the needs of psychosocially burdened families.

**Aims:**

The research project I-PREGNO aims to develop and evaluate a self-guided, smartphone-based intervention in combination with face-to-face counseling delivered by healthcare professionals for the prevention of unhealthy weight gain and psychosocial problems. The intervention is specifically tailored to the needs of psychosocially burdened families during the pregnancy and postpartum period.

**Methods:**

In two cluster randomized controlled trials in Germany and Austria (N = 400) psychosocially burdened families will be recruited and randomized to i) treatment as usual (TAU), or ii) I-PREGNO intervention (self-guided I-PREGNO app with counseling sessions) and TAU. We expect higher acceptance and better outcomes on parental weight gain and psychosocial stress in the intervention group.

**Discussion:**

The intervention offers a low cost and low-threshold intervention and considers the life situation of psychosocially burdened families who are a neglected group in traditional prevention programs. After positive evaluation, the intervention may easily be implemented in existing perinatal care structures in European countries such as Germany and Austria.

**Trial registration:**

Both trials were registered prospectively at the German Clinical Trials Register (Germany: DRKS00029673; Austria: DRKS00029934) in July and August 2022.

## Background

The perinatal period represents a critical period for the families’ health with biological, psychosocial, and behavioral changes and challenges. Due to health behavior changes (including changes in eating behavior, sleep behavior, physical activity and sedentary behavior) the transition to parenthood represents an inflection point for overweight and obesity, such that perinatal weight gains are retained in the long term [1, 2]. In Europe, three out of every four pregnant women gain more weight than recommended by the Institute of Medicine [3, 4]. Although many mothers loose this extra weight again at 12 months postpartum, about 20 – 50 % of women still face postpartum weight retention which contributes considerably to their risk of developing overweight and obesity [5, 6]. Perinatal unhealthy weight gain can also be observed in fathers [7]. Recent findings show that also fathers gain a significant amount of weight and fat mass during pregnancy, with some even gaining almost 10 kg [7, 8]. Maternal excessive gestational weight gain moreover has a negative influence on their offspring [9–11]. In addition, the postpartum period is also crucial for the offspring’s risk of developing chronic diseases, including obesity. The children’s risk for overweight and obesity depends on parental feeding practices, well-being and the mother-child relationship [12].

The main modifiable health or lifestyle behaviors contributing to unhealthy weight gain are dietary intake and physical activity [13]. Women and men experience different changes in dietary intake and physical activity throughout the perinatal period which can be explained by determinants at the individual, interpersonal, environmental and policy level [14–16]. Hence, existing gestational weight gain interventions often focus on eating behavior or physical activity [17]. Studies that have investigated both behaviors during the perinatal period show that psychological and social factors (e.g. emotion regulation, depression, social support) influence these lifestyle behaviors, especially during the perinatal period [18, 19]. In prevention programs that target pregnant women in order to prevent unhealthy perinatal weight gain, the underlying psychological factors have been barely considered [20]. Since the transition to parenthood represents a period in which parents often experience heightened psychosocial stress and symptoms of depression, sleeping disorders and anxiety [1], integrating strategies that promote the parental well-being and prevent psychosocial stress could increase the effectiveness of perinatal weight management interventions.

Psychosocially burdened families (e.g., families with low socio-economic status (SES), mental health problems) are particularly vulnerable to unhealthy gestational weight gain and weight retention after birth [21–24]. Yet, there is no monocausal pathway to unhealthy weight gain or health impairments in general, but socioeconomic burden is often linked to impaired health via cumulative risk exposure and poor health behavior or literacy [25–29]. Besides socioeconomic burden, also other psychosocial burden e g., depression, relationship distress or ineffective emotion regulation are considered as correlates or mediating mechanisms for unhealthy weight gain or overweight [30, 31]. However, little is known about the effectiveness of preventive interventions among these vulnerable groups since those families are often not reached by prevention programs and interventions – not even by digital ones [32–34]. Furthermore, the specific needs of psychosocially burdened families are often not taken into account in the development of new interventions. Hence, there is a clear need for preventive interventions that are specifically tailored to the needs and life situations of this vulnerable group.

In recent years, in the hope of reaching more individuals, especially those who cannot be reached through traditional counseling approaches, the development and implementation of mobile health (mHealth) interventions has emerged. Apps provide a low-threshold and inexpensive access, and could represent an added value to existing programs especially for time-restricted phases of life such as the pregnancy or perinatal period [35–37]. Today, almost everybody in Europe has a smartphone regardless of SES. Especially the current generation of expectant parents is familiar with digital tools and the acceptance rates of mHealth is extremely high compared to other target groups [38]. Hence, an app-based prevention approach is promising to reach the neglected group of psychosocially burdened families in prevention services. Furthermore, mHealth interventions seem to be even more promising if they are combined with personal contacts [39]. As preceding research suggests, an mHealth intervention tailored to individual needs in combination with successful face-to-face counseling might be particularly useful for reaching people with low SES [40, 41]. Despite such advantages of low-threshold supply of mHealth interventions, many recent lifestyle counseling and smartphone-based weight management interventions did not include individuals with psychosocial burdens in either pregnancy or the postpartum period [40, 42]. In addition, the majority of such interventions neglect fathers (to-be) and have a strong focus on maternal needs [40]. However, paternal involvement may increase intervention effects substantially by providing additional social and practical support for mothers (and the family) buffering the experienced stress during this challenging and vulnerable period of life [43].

Based on the challenges during COVID-19 and the fast-evolving digital change in the last decade, an mHealth based intervention could be an effective approach to prevent unhealthy weight gain and psychosocial stress in vulnerable families during the perinatal period. The intervention should initially focus on psychological factors known to be related to health behaviors affecting the perinatal weight gain, involve both parents, and should be extended over the complete perinatal period. As first of its kind, the overall objective of I-PREGNO is the development and evaluation of an mHealth intervention that aims to prevent unhealthy weight in psychosocially burdened families through the promotion of health behavior (i.e., eating behavior and physical activity), and the parental well-being during the perinatal period. I-PREGNO was developed from June 2021 to July 2022 and consists of a self-guided multicomponent smartphone app combined with face-to-face counseling that can be implemented into existing perinatal care services. In two cluster randomized controlled trials (cRCTs) we will examine the efficacy of the intervention in existing health and family care services during pregnancy and the postpartum period. We expect that our developed mHealth intervention has a positive effect on the prevention of unhealthy weight gain (indicated by a body mass index (BMI) that is more stable than in the control condition) during the pregnancy and postpartum period and promotes psychological competences (i.e., emotion regulation, self-efficacy) that reduce stress and poor mental health particularly in vulnerable families.

## Methods

The study design is reported in line with the SPIRIT 2013 Statement (Standard Protocol Items: Recommendations for Interventional Trials) [44]. The study has received ethical approval from the ethical committee of the University in Bamberg (nr. 2022-02/09) and of the Medical University in Graz (nr. 34-249 ex21/22). Both trials were registered in the German register for clinical trials (DRKS00029673; DRKS00029934).

### Overall study design

I-PREGNO is a multinational study, with two study centers in Germany and one study center in Austria. The trial’s design is a multicenter cRCT aiming to reduce the risk of unhealthy weight gain and promote the well-being of vulnerable families during the perinatal period. Due to the different healthcare structures, the study designs in both countries differ in some characteristics. Therefore, some parts of the trials are described separately in the following text. Figures 1 and 2 provide an overview of the study trials.

**Fig. 1 Fig1:**
[figure not shown]
CONSORT Flowchart for the trial in Austria during pregnancy and postpartum *Note.* HP = Healthcare professionals (midwives); TAU = treatment as usual

**Fig. 2 Fig2:**
[figure not shown]
CONSORT flowchart for the trial in Germany during the postpartum period *Note.* HP = Healthcare professionals (family midwives, family nurses and social workers); TAU = treatment as usual

### Setting

We will use a parallel two-arm cRCT design with one intervention group, receiving the I-PREGNO blended counseling intervention plus treatment as usual (TAU) and one control group with TAU only. *In Austria*, the trial will start during the second trimester of pregnancy and continue until the postpartum period. As we focus on psychosocially burdened families, our sample will be recruited mainly by midwives who have a contract with public healthcare operators. In *Germany*, we will investigate the efficacy during the first year postpartum. Our target group will be recruited within a nationwide *Early Childhood Intervention* program, particularly a selective prevention home-visiting program for psychosocially burdened families delivered by midwives and nurses with a special training, and in some federal states or municipalities also other professionals. All professionals are summarized under the term healthcare professionals (HPs) in the following text.

### Recruitment of Healthcare Professionals

HPs are supposed to recruit participants and conduct the blended counseling of the intervention in both countries. In *Austria*, the eligibility criteria of HPs are being a certified midwife within the Austrian public healthcare system, offering a counseling session during pregnancy and the postpartum period, and sufficient knowledge of the German language. To motivate HPs to participate in our study, we have worked closely with the clinical Department for Obstetrics and Gynaecology in Graz (Austria) as well as the midwifery committee of Austria. The study team of Graz will send advertising emails and conduct cold calls to promote the project.

In *Germany,* HPs within the national early childhood intervention program represent all individuals who are either in training or already have a degree as a family midwife or family nurse. Eligibility criteria are the support of at least one family who can be included in the study and sufficient German language skills. To motivate HPs to participate in our study, we have worked closely with the program’s coordination units in different federal states in Germany. They will promote I-PREGNO and will send advertising emails to all HPs in their state. In addition, the study team will offer online information events in which the intervention and the process of the study will be presented. Participating HPs in both countries will receive €50 for every family they recruit and that completes the baseline assessment.

### Participants

For a family to participate, at least the mother has to agree to participate in the study. If the father of a family is also present and agrees to participate, he can be registered separately by the HP. Families will be enrolled by the HP once the mother agrees to participate in the study.

*In Austria,* eligible families should a) meet one of the criteria of low SES (defined as: no partner or receipt of financial benefits or low education), b) expect a child (gestational age between the 18^th^ and 22^th^ week) and c) own a smartphone. *In Germany,* eligible families are those who a) meet at least one of the psychosocial burden factors (see Table 1), b) have a child at the age between 0-12 months, c) own a smartphone, and d) receive home-visiting support from a HP for a period of at least 12 weeks.

**Table 1 Tab1:** List of psychosocial burden factors as part for the inclusion criteria in Germany

**Psychosocial burden factors**	• financial problems • single parenthood • mental illness of one parent • underaged mother • insecure living situation • traumatic life events in the past • social isolation / lack of integration • birth of multiples and rapid succession of births • premature birth of the child • regulatory disorder of the child • chronical illness, developmental delay and/or disability of the child • relationship distress

In both countries, families will be excluded from the study if they meet at least one of the following exclusion criteria: a) mother is younger than 16 years; b) acute mental health problems that hamper the ability to participate (e.g., suicidality, mania); c) chronic disease that can influence behavior related to energy balance (diabetes, pre-eclampsia, etc.) or require a complex diet, d) insufficient knowledge of the German language (which does not allow the use of the app and the completion of the questionnaires) or e) other reasons that do not allow the correct use of the app, counseling or completion of the questionnaires. Each family will receive €50 for participation if all questionnaires are completed.

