### Sample size calculation

For the primary outcome (weight), we have calculated in G*Power that we need to recruit 100 families in each study arm, based on two-sided testing with alpha of 5%, and assuming 20% drop out in order to have at least 80% power to detect a 2 kg difference in weight gain/retention between intervention arms. This is based on the intervention effect on gestational weight gain of the DALI intervention (Simmons D: JCEM 2016), and assuming non-significant clustering in weight within HPs. With this sample size, a 0.45 (SD 1.0) difference in birthweight z-score or infant BMI z-score can be found with 80% power. Since both trials will initially be analyzed separately and assuming non-significant clustering in weight within HPs, clustering by country (Germany, Austria) is not considered in the sample size calculation. Based on previous exchange with HPs, we estimated 2-4 families per HP as realistic. Therefore we intend to recruit at least 60 HPs in each study arm.

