### Outcomes

Our primary outcome will be body composition measured through body mass index (BMI) of the family members (self-reported, the mother’s, if available father’s and the child’s height and weight). Secondary outcomes will be eating behavior (i.e., eating styles), physical activity, and psychological factors (i.e., depression, emotion regulation, parental stress) that are associated with the family’s well-being and influence eating behavior and physical activity. Information about the children (height, weight, breastfeeding) is collected through the mothers. Since the project primarily intends to reach psychosocially burdened families another focus lies on socio-demographic characteristics and socio-economic stressors (e.g., whether families receive social support, health status, crowded living conditions, and the migrant status of the parents). Data will be gathered at three (Germany) or four (Austria) time points. Tables 2 and 3 provide an overview of the included measurements.

**Table 2 Tab2:** Data collection at different time points during the study in Austria

Questionnaire	t_0_	t_0.5_	t_1_	t_2_
	18^th^ to 22^nd^ week of pregnancy	35^th^ -37^th^ week of pregnancy	8 weeks pp	3 months after t_1_
Socio-demographics	x			
Weight of the parent	x	x	x	x
Child’s weight and height			x	x
DEBQ	x	x	x	x
FFQ	x	x	x	x
IPAQ	x	x	x	x
EPDS	x	x	x	x
DERS-SF	x	x	x	x
ECR-RD		x		
GSE	x	x	x	x
CTS		x		
PSI-SF			x	x
PBQ			x	
I-FEEL				x
Regulatory Disorders				x
MAUQ			x	

*DEBQ* Dutch Eating Behaviour Questionnaire, *FFQ* Food Frequency Questionnaire, *IPAQ* International Physical Activity Questionnaire, *EPDS* Edinburgh-Postnatal-Depression-Scale, *DERS-SF* Difficulties in Emotion Regulation Scale, *ECR-RD* Experiences in Close Relationships, *GSE* General Self-Efficacy Scale, *CTS* Childhood Trauma Screener, *PSI-SF* Parenting Stress Index, *PBQ* Postpartum Bonding Questionnaire, *MAUQ* mHealth app usability questionnaire, *pp* postpartum

**Table 3 Tab3:** Data collection at different time points during the study in Germany

Questionnaire	t_0_	t_1_	t_2_
	0-12 months pp	3-15 months pp	3 months after t1
Socio-demographics	x		
Weight of the parent	x	x	x
Child’s weight and height	x	x	x
DEBQ	x	x	x
FFQ	x	x	x
IPAQ	x	x	x
EPDS	x	x	x
DERS-SF	x	x	x
ECR-RD		x	
GSE	x	x	x
CTS	x		
PSI-SF	x	x	x
PBQ	x	x	x
I-FEEL			x
Regulatory Disorders			x
MAUQ		x	

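### The German trial neither excludes mothers who are pregnant again at baseline nor lists a measure of a new pregnancy, so gestational gain can be counted as postpartum weight gain or retention

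*Protocol article*

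**What the plan says.** **Entry (Protocol article, Participants).** A German family must "have a child at the age between 0-12 months", show at least one burden factor from Table 1, own a smartphone and receive home visits for at least 12 weeks. Table 1 has twelve entries, one of which is "birth of multiples and rapid succession of births".

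**Exclusions (Participants).** One list, a) to e), serves both countries. Apart from maternal age, acute mental health problems and language, it names "chronic disease that can influence behavior related to energy balance (diabetes, pre-eclampsia, etc.) or require a complex diet" and "other reasons that do not allow the correct use of the app, counseling or completion of the questionnaires". A current pregnancy is not named. It could not be named in a shared list, because the Austrian trial enrols pregnant women.

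**Outcome (Outcomes).** "Our primary outcome will be body composition measured through body mass index (BMI) of the family members". It is self-reported and includes the mother's weight.

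**Assessments (Procedure; Table 3).** t1 comes 12 weeks after baseline, at 3-15 months postpartum, and t2 three months after t1. Table 3 lists parental weight at all three times and socio-demographics at t0 only. No entry concerns a new pregnancy.

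**Power (Sample size calculation).** 100 families per arm, "assuming 20% drop out in order to have at least 80% power to detect a 2 kg difference in weight gain/retention between intervention arms", with a two-sided alpha of 5%. No SD for weight is given.

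**Analysis (Statistical analyses).** Intention to treat, adjusted for the baseline value of the outcome.

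**The concern.** The German trial asks about weight in the postpartum period. The Background says success will show as a BMI that stays more stable than under control. Weight gained in a new pregnancy is neither instability nor retention in that sense, yet a self-reported BMI cannot tell them apart.

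Under the eligibility text, a mother with an 11-month-old who is already 16-20 weeks pregnant can enter. Others may conceive between t0 and t2, which for the latest entrants falls about 18 months after the index birth. Exclusion c) removes conditions that act on energy balance, so leaving in a state that changes weight directly is hard to square with the plan's own aim.

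Baseline adjustment takes account of weight gained before t0 but not of gain after it. An analysis plan can add a handling rule later, but it can apply that rule only if pregnancy status was collected. Eligibility and data items therefore have to be settled before data collection.

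**Working it through.** **Step 1: can a new pregnancy enter?** Exclusion c) concerns chronic disease or a complex diet. Exclusion e) is a catch-all limited to using the app, the counseling or the questionnaires. Criteria a), b) and d) are unrelated. So yes, both at t0 and during follow-up. The latest follow-up is 12 months at entry + about 3 months to t1 + 3 months to t2 = about 18 months postpartum.

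**Step 2: the plan's own figures.**
- 100 per arm less 20% dropout leaves 80 per arm.
- The statement with a full set of inputs (0.45, SD 1.0, 80% power) gives n = 2 × (1.960 + 0.842)² / 0.45² = 77.5, so 78 per arm. 78 / 0.8 = 97.5, so 98 against the stated 100. It reproduces.
- The 2 kg statement has no SD, so it can only be solved backwards: SD = 2 / (2.802 × √(2/80)) = 4.515 kg. A t-based calculation gives a standardized difference of about 0.446 and SD = 2 / 0.446, about 4.49 kg.
- With SD 4.515 the standard error of the difference is 4.515 × √(2/80) = 0.714 kg, and power is 80%.

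**Step 3: assumed size of the gain.** The documents give none. At an assumed 0.4-0.5 kg per week in mid to late pregnancy, 12 weeks gives 4.8-6 kg, or 2.4-3 times the 2 kg target. I use 5.5 kg below.

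**Step 4: added variance.** If a share q of mothers in both arms carries g kg extra, the variance rises by q(1 − q)g². Power is Φ(2 / (SD × √(2/80)) − 1.960).

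| q (assumed) | Added variance, g = 5.5 kg | New SD from 4.515 (from 4.49) | Power from 4.515 (from 4.49) |
|---|---|---|---|
| 0 | 0 | 4.515 (4.49) | 80.0% (80.4%) |
| 2% | 0.02 × 0.98 × 30.25 = 0.593 | 4.58 (4.56) | 78.9% (79.3%) |
| 5% | 0.05 × 0.95 × 30.25 = 1.437 | 4.67 (4.65) | 77.3% (77.7%) |

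**Step 5: a wider range.** With the same formula and base SD 4.515, still on assumed inputs of 3 to 10 kg extra:
- q = 2%: power 79.7% down to 76.3%.
- q = 5%: power 79.2% down to 71.3%.
- q = 10%: power 78.5% down to 64.6%.

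The lowest figure needs one mother in ten affected and 10 kg each, for which the documents offer no support.

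**The case against.** Several objections have force.

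**Enrichment.** A reader might infer from Table 1 that the trial selects mothers likely to conceive again soon. The text does not support that. The entry describes births that have happened, is half of one of twelve alternative factors, and nothing says how many mothers enter through it.

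**Irrecoverable status.** A reader might also infer that affected mothers could never be identified later. That goes too far. Table 3 lists instruments, not items; the socio-demographic block includes health status among its examples; the professionals complete surveys on inclusion and exclusion criteria; and German usual care normally means weekly home visits. An unprinted item may exist. What stands is narrower: no listed measure records a new pregnancy, and the socio-demographic block is shown at t0 only.

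**Bias through imbalance.** Four extra pregnant mothers among 80 in one arm would move the contrast by 4/80 × 4.8-6 kg = 0.24-0.30 kg. It is tempting to add this to the loss of power. But it is only 0.34-0.42 of the standard error (0.714 kg): ordinary random error, already contained in the larger SD. Professionals do know their allocation when they screen, so differential enrolment is possible, but nothing in the documents shows it.

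**Size.** The rate and the gain are both assumed, and a full 12 weeks of mid-to-late gain is near the worst case. Mothers with very young infants cannot be that far into a new pregnancy, and those who conceive after t0 spend the interval to t1 in early pregnancy. Mothers are also only one part of an outcome that covers fathers and children.

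**Scope.** How to treat weights after conception is usually left to an analysis plan, so the lack of a rule in this article is not the finding. Admitting pregnant mothers could also be a deliberate choice, since the app has pregnancy and postpartum modes. However, the article states no such intention for Germany, and the outcome is not defined to allow for it.

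**Conclusion.** The point holds in a limited form. The German eligibility text admits mothers who are already pregnant again, and no listed measure records a new pregnancy, so gestational gain can enter the primary weight/BMI outcome as postpartum gain or retention. The main consequences are a less clear outcome and added noise. Randomization gives no reason to expect systematic bias.

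The size cannot be derived from the documents. It rests on 80 analysed mothers per arm, a back-solved SD of about 4.5 kg, an equal assumed share of 2-5% in both arms, and an assumed 5.5 kg each. On those assumptions power falls from about 80% to about 77-79%. That is modest, but the planned sample leaves almost no slack and the remedy is cheap. The case does not depend on the Table 1 entry about closely spaced births.

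**What to change.** 1. **Eligibility.** Add current pregnancy at t0 as an exclusion for Germany only, leaving the shared list as it is for Austria. The professionals' existing survey on inclusion and exclusion criteria can carry it.
2. **Data.** Add one pregnancy-status item to the German mother's questionnaire at t0, t1 and t2, unless the full questionnaire already holds one. It should date conception well enough to tell which weights follow it.
3. **Analysis.** Keep mothers who conceive after t0 in the intention-to-treat set. Beside the analysis of all weights, report a prespecified sensitivity analysis in which weights after conception are set to missing and imputed. This can sit in the analysis plan, provided item 2 is in place before data collection.

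The cost is one eligibility line and one question. A few families become ineligible, a real but small loss in a group that the Discussion calls difficult to reach.
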